#### Interim analyses {21b}

A data and monitoring safety board (DSMB) will monitor ongoing results to ensure patient well-being and safety as well as study integrity. The DSMB will be asked to recommend early termination or modification only when there is clear and substantial evidence of a safety issue.

#### Methods for additional analyses (e.g., subgroup analyses) {20b}

Subgroup analyses for the primary and selected secondary outcomes will evaluate the treatment effect across the following subgroups: duration of symptoms prior to enrolment, age groups, disease severity at baseline, and comorbidities. A forest plot will display confidence intervals across subgroups. Interaction tests will be conducted to determine whether the effect of treatment varies by subgroup.

#### Methods in analysis to handle protocol non-adherence and any statistical methods to handle missing data {20c}

All efficacy analyses are based on the intention-to-treat principle and are performed on the Full Analysis Set (FAS). The FAS includes all randomized patients according to their randomized treatment. However, COVID-negative patients who were mistakenly randomized will be omitted from the FAS. Missing clinical status data will be accounted for by multiple imputation methodology using a total of 100 imputations [22].

Patients from the FAS with major protocol violations will be excluded from the Per Protocol Set (PPS). The PSS will be reviewed and finalized at the Blind Review Meeting just prior to database lock.

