### Eligibility criteria {10}

In short, participants eligible for inclusion are adult patients, hospitalized with COVID-19 disease. This means they have confirmed SARS-CoV-2 infection (either diagnosed with PCR or a typical pattern on chest CT) and disease signs (either clinical or radiological). Inclusion and exclusion criteria are summarized below; the fully detailed criteria are listed in the protocol (see Additional file 1).

Inclusion criteria:
Male or non-pregnant female adult ≥ 18 years of age at time of enrolmentHas a confirmed diagnosis of SARS-CoV-2 infection within 72 h prior to randomization, defined as either:
Laboratory-confirmed SARS-CoV-2 infection as determined by PCR, or other commercial or public health assay in any specimenorThe combination of upper or lower respiratory infection symptoms (fever, cough, dyspnea, desaturation) and typical findings on chest CT scan, and absence of other plausible diagnosesIllness of any duration, and at least one of the following:
Radiographic infiltrates by imaging (chest x-ray, CT scan, etc.), orClinical assessment (evidence of rales/crackles on exam) AND SpO2 ≤ 94% on room air, orRequiring mechanical ventilation and/or supplemental oxygenAdmitted to specialized COVID-19 ward or an ICU ward taking care of COVID-19 patients

Exclusion criteria:
ALT/AST > 5 times the upper limit of normalPregnancy or breast feedingAllergy to any study medicationAny medical condition which would impose an unacceptable safety hazard by participation to the studyHeart failure with severely reduced ejection fraction (≤ 30%)Known prolonged QT interval on ECG (> 470 ms males and > 480 females according to the Fridericia formula for corrected QT, or—in patients with ventricular conduction delay—the Rautaharju formula)Patients on macrolides during the last week before admission

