### Assignment of interventions: blinding

#### Who will be blinded {17a}

The study is open label. Patients, clinicians, and study personnel are aware of the assigned treatment. The trial statistician was not given access to the full database and was not aware of the allocated treatments. The trial statistician will remain blinded until database lock.

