##### Other investigations

The study includes optional measurements on day 6 (± 2) on the condition that this does not hinder routine clinical care: an additional assessment (e.g., nasopharyngeal swab) for SARS-CoV-2 with both quantitative and qualitative PCR.The study includes two optional blood samples: One additional serum tube will be obtained within the first week after diagnosis, and one at the ambulatory visit of 5 to 7 weeks after discharge. The time window for the first sample taking is deliberately wide, to easily combine this with a blood drawing performed for the clinical routine, and thus minimize the burden for caregivers and patients, and avoid the waste of personal protective equipment.The study includes a QTc assessment on ECG (days 2–3) or continuous ECG monitoring during administration of the study drug in patients on ICU, considering potential co-treatment with QTc prolonging drugs as listed in the appendix of the protocol.

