### Statistical methods

#### Statistical methods for primary and secondary outcomes {20a}

Hereby provided is a summary of the most important statistical analyses. Further details will be outlined in the SAP that will be finalized before database lock.

This open-label controlled randomized trial tests a superiority hypothesis with a two-sided type I error rate of 0.05. Secondary hypotheses of this exploratory study will be tested in a non-hierarchical way. These will be described according to the appropriate summary statistics (e.g., proportions for categorical data, means with 95% confidence intervals for continuous data, median for time-to-event data).

The primary outcome is based on an ordinal severity scale with 7 categories. This scale has been proposed by the WHO for COVID-19-related research and has been previously used in trials of patients with influenza. Previously reported studies and ongoing studies record the same primary outcome, which allows cross-study data pooling. The primary endpoint will be analyzed by means of competing risk analyses whereby death without any improvement will be considered as a competing risk. Event rates will be estimated using cumulative incidence functions (CIF). Median times to improvement will be calculated by the treatment group. The effect of treatment will be assessed by performing a Fine and Gray competing risk regression model that includes the baseline value on day 0 as a covariate and randomized treatment as a factor. From the Fine and Gray model, the subdistribution hazard ratio and associated 95% confidence interval will be estimated.

Secondary endpoints will be analyzed as follows:

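### The FAS is described as intention-to-treat on all randomized patients but omits some of them, under a rule not tied to pre-randomization evidence or to judgement blind to arm

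*Protocol article*

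**What the plan says.** Section {20c} of the protocol article makes three statements in succession:

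- It first sets the principle: "All efficacy analyses are based on the intention-to-treat principle and are performed on the Full Analysis Set (FAS".
- It next says who belongs to that set: "The FAS includes all randomized patients according to their randomized treatment".
- It then makes an exception: "COVID-negative patients who were mistakenly randomized will be omitted from the FAS".

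The per-protocol set is then formed by taking FAS patients with major violations out, and it is this set that is to be "reviewed and finalized at the Blind Review Meeting just prior to database lock".

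Four other places bear on the rule:

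- **Eligibility criteria {10}:** infection may be established by two routes, "either diagnosed with PCR or a typical pattern on chest CT". The CT route also needs respiratory symptoms and no other plausible diagnosis. Both routes are tied to the 72 hours before randomization.
- **Concealment mechanism {16b}:** the investigator learns the allocation as soon as inclusion is confirmed.
- **Who will be blinded {17a}:** "Patients, clinicians, and study personnel are aware of the assigned treatment". Only the trial statistician is blinded, until database lock.
- **Statistical methods {20a}:** the trial "tests a superiority hypothesis with a two-sided type I error rate of 0.05".

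**The concern.** The third statement in {20c} takes back what the first two promise. All efficacy analyses use the FAS and the per-protocol set lies inside it, so a patient dropped from the FAS appears in no efficacy analysis that the article describes. The primary result would be labelled intention-to-treat without being an analysis of all randomized patients.

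Excluding patients after randomization can be harmless if the reason was fixed before allocation and is judged without knowledge of arm. The stated rule imposes neither condition, and the people who make diagnoses at the sites know the allocation. If later work-up influenced who counts as COVID-negative, and did so differently by arm, the primary comparison would lose the protection of randomization. The Discussion already concedes that the open-label design carries observation and performance bias.

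**Working it through.** **1. The analysis sets side by side**

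- FAS = all randomized patients minus the omitted COVID-negative patients.
- Per-protocol set = FAS minus major violators.
- Efficacy analyses = FAS (all of them), with the per-protocol set as a subset.
- Efficacy analyses containing every randomized patient = none named.

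This step needs no assumptions.

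**2. What the exclusion rule requires**

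A patient must be COVID-negative and must also have been randomized by mistake. A patient who met the CT route on entry was validly enrolled and fails the second condition. However, the CT route depends partly on there being no other plausible diagnosis. That judgement can be overturned later, after which the patient could be called both COVID-negative and mistakenly enrolled. The rule does not exclude this reading, and it does not prescribe it either.

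**3. The plan's own sample-size figure**

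Inputs from Sample size {14}: control 40% at day 15, improvement 17.5 points (57.5%), 2:1 allocation, 80% power, two-sided 5%.

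- Hazard ratio = ln(1 − 0.575)/ln(1 − 0.40) = 1.675.
- Events (Schoenfeld) = (1.96 + 0.8416)² / [(1/3)(2/3)(ln 1.675)²] = 133 after rounding up.
- Mean event probability = (0.40 + 2 × 0.575)/3 = 0.517.
- N = 133/0.517 = 257.4, so 258, as stated.

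The same method gives 354 for 15 points (stated 354) and 195 for 20 points (stated 196). The sample size is not in dispute.

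**4. What exclusions cost in power**

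The planned 282 leaves 282 − 258 = 24 patients (8.5%) of margin for all losses. The article gives no expected share of COVID-negative patients, so 2% to 15% is assumed here. Power at 17.5 points, with no other loss:

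| Share of 282 removed | Power |
|---|---|
| 0% | 83.5% |
| 2% | 82.8% |
| 5% | 81.6% |
| 10% | 79.5% |
| 15% | 77.2% |

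**5. When the exclusion would bias the comparison**

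Assumptions: no true effect, 40% improvement in both arms, 188 versus 94 randomized (282 split 2:1), a share f removed from an arm, and 80% improvement among those removed. Only the 40%, the 282 and the 2:1 ratio come from the article. The rate left in an arm is (0.40 − 0.80f)/(1 − f). Type I error is from a two-proportion z-test at 1.96.

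| Removed, azithromycin vs control | Rates left | Shift (points) | Type I error |
|---|---|---|---|
| 5% vs 5% | 0.379 vs 0.379 | 0 | 0.050 |
| 10% vs 5% | 0.356 vs 0.379 | −2.3 | 0.066 |
| 5% vs 10% | 0.379 vs 0.356 | +2.3 | 0.066 |
| 10% vs 2% | 0.356 vs 0.392 | −3.6 | 0.090 |
| 2% vs 10% | 0.392 vs 0.356 | +3.6 | 0.088 |

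If removed patients improve at the same 40% as everyone else, 10% versus 5% removal gives no shift and a type I error of 0.050. In these scenarios bias needs both conditions together: removal that differs by arm, and removal that is related to outcome.

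**The case against.** The best defence is that the exception is narrow, pre-specified and disclosed directly after the FAS definition. Read naturally, it covers patients who failed an entry criterion that is itself tied to the 72 hours before randomization. Excluding on such facts, in the same way in both arms, does not bias the comparison. The statistician is blinded and a blind review precedes database lock. Who judges, when and on what evidence is detail that an article may leave to the full protocol or SAP.

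Much of this stands. Three stronger readings are tempting, and the article does not support them:

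- **That the rule removes validly enrolled CT-diagnosed patients who are PCR-negative.** Such patients meet Eligibility criteria {10}, so they were not randomized by mistake. Their removal is a risk of loose wording, not a stated rule.
- **That the day-6 PCR decides FAS membership.** Under Other investigations, "The study includes optional measurements on day 6 (± 2" days) are described as optional, and the outcomes list treats the swab as exploratory. Nothing links it to the analysis sets.
- **That unblinded staff apply the exclusion.** The article does not say who applies it.

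The defence does not remove the conflict in {20c}. That concerns what the article states, not a detail it leaves out: the set called all randomized patients is not that set, and no all-randomized efficacy analysis is named. Blind review is stated for the per-protocol set and is not extended to this exclusion.

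**Conclusion.** The point holds in limited form. The departure from the stated intention-to-treat set is plain from the text and rests on no assumption. The route to bias is conditional: the wording permits an exclusion informed by post-allocation evidence in an open-label trial, but the article neither says this will happen nor gives a reason to expect it to differ by arm.

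The size of any bias cannot be derived from the document, because the number of patients affected, their outcomes and their split by arm are all unknown. The shifts of 2.3 and 3.6 points are illustrations under assumed inputs, to be read against a design difference of 17.5 points. The effect on power is small while total losses stay within the 24-patient margin. The change is worth making because it protects the primary comparison at very little cost, not because harm has been shown.

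**What to change.** Run the primary analysis on all randomized patients in their allocated arms, and move the COVID-negative exclusion to a sensitivity analysis or to the per-protocol set.

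If the sponsor keeps the exclusion in the FAS, section {20c} should:

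- limit it to patients who met neither the PCR nor the CT route of Eligibility criteria {10} on evidence obtained before randomization;
- have it decided blind to arm, for which the Blind Review Meeting already planned would serve;
- report an all-randomized analysis alongside.

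The cost is one sentence in the analysis-set definition and one additional analysis. No sample-size figure changes. Keeping true non-cases dilutes the effect slightly. If they are spread equally over the arms and gain nothing from treatment, a 17.5-point difference becomes 17.5 × 0.98 = 17.15 points with 2% non-cases and 17.5 × 0.95 = 16.6 points with 5% (both shares assumed).

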### Primary outcome

The primary outcome is the time from admission/randomization (day 0) to sustained clinical improvement or live discharge, whichever comes first, whereby a sustained clinical improvement is defined as an improvement of > 2 points vs the highest value of day 0 and 1 and sustained for at least 3 days.

The clinical status is recorded on a 7-point ordinal scale:
Not hospitalized, no limitations on activities;Not hospitalized, limitation on activities;Hospitalized, not requiring supplemental oxygen;Hospitalized, requiring supplemental oxygen;Hospitalized, on non-invasive ventilation or high flow oxygen devices;Hospitalized, on invasive mechanical ventilation or ECMO; andDeath.

This ordinal scale was chosen in compliance with the WHO master template and to facilitate data pooling with other studies. A 2-point improvement has been used in other COVID trials [20] as a robust and clinically relevant outcome. Concretely, in clinical practice, this 2-point improvement implies that a patient who is admitted to the ICU has at least been downgraded to a non-intensive care ward, and a patient who was admitted to the hospital on a normal ward has been discharged.

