#### Sample size {14}

As in other COVID trials [20], the time to reach a 2-point improvement on the WHO ordinal scale was chosen as the primary outcome. While azithromycin is generally safe, some concerns have been raised with the large-scale use in COVID-19, e.g., a possible increase of cardiac adverse events when combined with other QT-prolonging drugs such as hydroxychloroquine or increased bacterial resistance. While the exact proportions of such harms are not yet clear, we deemed that a sufficiently low number needed to treat was necessary to outweigh these potential risks and for the trial results be truly clinically meaningful. An absolute risk difference of 15 to 20% (correlating to a single-digit number needed to treat [NNT] between 7 and 5) therefore seemed appropriate. In concrete clinical terms, this means the following: Based on the control group of the Lopinavir-Ritonavir trial of Cao et al. [20] that used the same ordinal scale and had a similar population, we can assume a 2-point improvement on the ordinal scale will be observed in 40% of patients with standard of care at day 15. An absolute risk difference of 15% or 20% means that respectively 55% or 60% instead of 40% will have reached the primary endpoint in the azithromycin-treated group at day 15.

Based on the log-rank test, with a 2-sided significance level of 5 and 80% statistical power and using a (2:1) randomization ratio in favor of azithromycin, a total sample size of 354 patients would suffice to detect an absolute risk difference of 15%. To detect an absolute risk difference of 20%, a total sample of 196 patients would suffice. We propose a pragmatic sample size of 282 patients taking into account early dropouts. Two hundred fifty-eight patients will be sufficient to detect an absolute improvement of 17.5% with a statistical power of 80% at a 2-sided significance level of 5%.

Although it should be balanced against potential harms, we acknowledge that a larger NNT might also still be clinically relevant due to the scale of the pandemic. This emphasizes the importance of adhering to internationally promoted outcome measures like the WHO ordinal scale, to facilitate data pooling afterwards.

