##### Daily assessments until discharge

Administration of study drugVital signs (National Early Warning Score: BP syst, BP diast, HR, T°C, SPO2 (%), RR, O2 supplement (L/min), AVPU score)Clinical data collection for assessment of study outcomesTargeted medication reviewAdverse event evaluation

Serious adverse event and adverse event grades 4 and 5 will be collected when these are not outcomes of the study. When study-related procedures impose an additional burden on the clinical care of patients, they can be waived.

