##### Visit at days 15 (± 2) and 29 (± 3)

These visits can be phone visits when patients are no longer hospitalized or when safety issues do not permit physical contact. Primary and secondary outcomes are systematically assessed with standardized worksheets provided by the sponsor (complete set of worksheets can be provided on request).

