Cumulative clinical status up to day 15 will be analyzed using a general linear model adjusted for clinical status on day 0. The treatment effect will be estimated by the difference of mean values between the groups.Cumulative clinical status recorded daily during the hospital stay and on days 15 and 19 will be analyzed by means of a proportional odds logistic regression model, adjusted for clinical status on day 0. The treatment effect will be estimated by the common odds ratio.All-cause mortality rates will be estimated by treatment group using the Kaplan-Meier method. The resulting Kaplan-Meier curves will be compared using a log-rank test. The treatment effect will be estimated by the hazard ratio using a Cox regression.Other time-to-event parameters with competing risk: event rates will be estimated using cumulative incidence functions (CIF), and the resulting CIF curves will be compared using Gray’s test. The treatment effect will be estimated by the subdistribution hazard ratio.Duration of hospital and ICU stay: both parameters will be analyzed as time-to-event parameters with competing risk, whereby the event of interest is discharge from hospital/ICU and the competing risk is hospital/ICU death.Continuous normally distributed variables (e.g., QTc) will be analyzed using a 2-sample *t* test. Treatment effects will be estimated by the difference in mean values between the groups. If applicable, changes from baseline will be calculated. Comparisons between treatment groups will be done by performing an analysis of covariance (ANCOVA) on the post-baseline value, using the baseline value as a covariate.Continuous non-normally distributed variables (clinical status, NEWS score, duration of supplemental oxygen, duration of mechanical ventilation) will be analyzed using a Wilcoxon rank-sum test. Change in ordinal scale at specific time points will be compared using Wilcoxon rank-sum tests.

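### The day 1–15 sum score needs post-discharge days that are not recorded, and the only stated rule, general multiple imputation, could bias the treatment difference toward zero

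*Protocol article*

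**What the plan says.** All references are to the protocol article.

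- **Recording.** Under Secondary outcome, ordinal status is assessed each day in hospital and then on days 15 and 29. Clinical data collection sits under the heading "Daily assessments until discharge", and the participant timeline agrees. For the day 15 and day 29 contacts, "These visits can be phone visits when patients are no longer hospitalized".
- **Endpoint.** Secondary outcome defines cumulative clinical status as the sum of the daily scores for days 1 to 15. Section {20a} fixes the model: "Cumulative clinical status up to day 15 will be analyzed using a general linear model adjusted for clinical status on day 0", with the difference in means as the effect measure. Section {20a} also plans a proportional-odds model for the daily status.
- **Scale.** Under Primary outcome, the two lowest categories are "Not hospitalized, no limitations on activities" and "Not hospitalized, limitation on activities". Categories 3 to 6 are all inpatient states, and 7 is death.
- **Missing data.** Section {20c}: "Missing clinical status data will be accounted for by multiple imputation methodology using a total of 100 imputations". No other rule for unrecorded clinical status is given, and no exception is made for days after discharge or death.

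**The concern.** A patient discharged before day 14 has, by schedule, days inside the sum with no recorded status. These gaps arise because the patient improved, and their value is almost known: 1 or 2 by definition of the scale. Days after death are known exactly.

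The rule in {20c} does not separate such days from a status that is truly unknown. On days 1–14 nearly every recorded score comes from someone still in hospital or dead. The exception is a day-15 contact made early in its ±2-day window, on day 13 or 14. A model fitted to those scores would place discharged patients among inpatients. The arm with more early discharges would receive more of these too-high values, so the difference in means would move toward zero. The daily proportional-odds analysis has the same exposure. The primary endpoint does not, because discharge and death are handled there as events.

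**Working it through.** **1. The plan's own figures.** The article gives no figure for the sum score. Its day-15 scenario comes from Sample size {14}: the plan assumes that "a 2-point improvement on the ordinal scale will be observed in 40% of patients with standard of care at day 15", and it powers 258 patients for a gain of 17.5 points (57.5%). That figure reproduces with the Schoenfeld formula at 2:1, two-sided 5%, 80% power:

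- HR = ln(1 − 0.575)/ln(1 − 0.40) = 1.675
- events = (1.96 + 0.84)² / [(2/3)(1/3)(ln 1.675)²] ≈ 133
- mean event rate = (2 × 0.575 + 0.40)/3 = 0.517
- N = 133/0.517 ≈ 257, against 258 stated. The 15- and 20-point cases give 354 and 195, against 354 and 196.

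**2. How many days are involved.** Assume constant hazards, every event a discharge, and no deaths. Then λ = −ln(1 − p)/15, mean days before the event = p/λ, and post-discharge days = 15 − p/λ.

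- Control: λ = 0.03405; 0.40/0.03405 = 11.75; 15 − 11.75 = 3.25 days
- Azithromycin: λ = 0.05705; 0.575/0.05705 = 10.08; 15 − 10.08 = 4.92 days
- Imbalance: 4.92 − 3.25 = 1.67 days per patient. This is somewhat high, since some events are step-downs within hospital and day 15 itself is recorded.

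**3. Mechanism.** If the imputed mean is alike in both arms, the bias toward zero is about (imputed mean − true mean) × (difference in post-discharge days).

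**4. Regression imputation.** A daily 7-point course was simulated for 3,000 control and 6,000 treated patients in four scenarios. All transition rates were assumed. Discharge by day 15 was 46–68% in control and 58–84% in treated. Days 1–14 after discharge were blanked, day 15 was kept, and five imputations were used per variant. The true differences in the sum were −3.8 to −7.3 points. Unrestricted imputation gave post-discharge days a mean of 3.1–3.5, against a true mean of about 1.5.

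| Imputation of post-discharge days | Retained | Lost |
|---|---|---|
| Day 15 not a predictor | 47–66% | 34–53% |
| Day 15 a predictor | 49–53% | 47–51% |
| Treatment left out of the model | 40–46% | 54–60% |
| Held to 3–7 | 38–45% | 55–62% |
| Held to 1–2 | 87% | 13% |
| Day-15 status carried back | 100% (by construction) | 0% |

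Hand check of step 3, with day 15 as a predictor:

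- Blank share 25.6% and 34.1% of 14 days = 3.58 and 4.77 days, difference 1.19. Excess score 3.08 − 1.5 = 1.58. Product 1.88; simulated loss 3.76 − 1.84 = 1.92.
- Blank share 32.2% and 48.8% = 4.51 and 6.83 days, difference 2.32. Excess 3.09 − 1.51 = 1.58. Product 3.67; simulated loss 7.29 − 3.70 = 3.59.

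**5. A harsher model.** At the plan's rates (172 vs 86 patients), assume inpatient scores constant until discharge, every event a discharge, and 0–20% mortality by day 15. The true difference is −4.7 to −5.0 points. A single draw from same-day, same-arm inpatients leaves −0.5 to −0.9 (83–90% lost). Setting every blank day to 3 leaves −2.3 to −2.7 (46–50% lost). Power at 0, 10 and 20% mortality is 62, 53 and 43% with true scores, 23, 14 and 12% with inpatient draws, and 58, 36 and 29% with all 3s. These power figures rest on one draw, not on pooled imputations. Once step-down within hospital is allowed, the loss is 41–59%. It is about 0% if days are held to 1–2.

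**The case against.** The strongest reply is that nothing in the article calls post-discharge days missing. The scale already places such a patient at 1 or 2 and a dead patient at 7, and discharge and death times are collected. A sensible reading is that imputation covers only status that is truly unknown. The article is also a condensed account, and {20a} says: "Further details will be outlined in the SAP that will be finalized before database lock". The imputation model, its bounds and its predictors properly belong there, and their absence here is no fault. The endpoint is one of many secondary outcomes in a study described as exploratory.

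Much of this stands. A reader might infer that discharged patients will be given inpatient scores and that most of any benefit will disappear. The documents do not support that. They name no imputation model, and the loss varies from none to about 90% with the model chosen. The 83–90% figure needs draws that ignore the day-15 status, together with inpatient scores that never change. The latter puts all the benefit after discharge, whereas the Primary outcome section itself describes improvement from ICU to ward, which is recorded daily.

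The reply does not remove the point that the protocol has already fixed a general rule and the number of imputations. As worded, the rule reaches days whose value is bounded by definition. An SAP that followed it literally could produce the bias, and one that avoided it would need an exception the protocol does not make.

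**Conclusion.** The concern holds as an exposure created by the scope of a stated rule. If {20c} is applied without limits to post-discharge days, the sum-score difference is biased toward no effect by roughly one third to three fifths under regression imputation with the assumptions above. The loss is greater under same-day inpatient draws and 0–13% if the score is held to 1–2 or carried back from day 15. The direction follows from the schedule and the scale whenever azithromycin shortens stay. The size rests on assumed transition rates, an equal split between scores 1 and 2 after discharge, and the imputation model. The daily proportional-odds analysis shares the exposure. The primary endpoint and its sample size are untouched. This should be corrected before database lock but does not threaten the main result.

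**What to change.** In {20a} and {20c}, and in the SAP:

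- State that days after live discharge and days after death are not missing clinical status.
- Score each day from discharge to day 14 as 1 or 2, using the category reported at the day-15 contact. If that contact is missing, impute between 1 and 2 only.
- Use the inpatient category for known readmission days.
- Score 7 from the day of death.
- Restrict the 100 imputations to in-hospital days with no recorded status and to patients lost to follow-up.
- Use the completed scores in both the sum-score model and the daily proportional-odds model.

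The cost is a few sentences and one derivation step, because discharge and death dates and the day-15 contact are already planned. The small downside is that the distinction between 1 and 2 before day 15 is carried back, an error of at most 1 point per day.
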